### Recruitment {15}

Identifying those at risk of suicide is a core objective in national strategies to prevent suicide. Unfortunately, YEH have limited access to medical care and mental health services and are thus unlikely to be screened for suicide in traditional settings. More efforts are needed to identify YEH at risk for suicide and link them to appropriate resources. Therefore, in this study, 50% of the sample will be engaged from the local drop-in center, and 50% of the sample will be non-service-connected recruited through outreach in non-service locations. The outreach worker will engage and screen youths to determine basic eligibility for the study. Those engaged on the streets who meet preliminary eligibility will be transported to the drop-in center. The interviewer will review the nature and conditions of the study, and the informed consent/assent. After signing the consent/assent statement, the interviewer will administer the SSI-W instrument to determine formal eligibility. Those meeting the criteria for participation in the study (score 5 or higher at the SSI-W instrument) will continue with the study. Those not passing inclusion criteria for the project will be provided a care package (with toiletries and food items) and told that even though they are not eligible to participate in the current study, they can continue to receive services through the drop-in center. Those determined to be at imminent risk for suicide will be accompanied to the local emergency room. They can be eligible for the project when they indicate that they are no longer at imminent risk for self-harm.

## Assignment of interventions: allocation

### Sequence generation {16a}

At the end of the baseline assessment, we will use an urn randomization computerized program to ensure that the two study conditions are balanced by baseline service connection and other moderating variables (sex at birth, race, identify as sexual minority).

### Concealment mechanism {16b}

Upon completion of the baseline assessment, the RA contacts the PI with randomization information, and the PI randomizes the client using the computerized urn randomization program.

### Implementation {16c}

RAs enroll participants and the PI assigns each participant to a condition based upon the urn randomization program results.

## Assignment of interventions: blinding

### Who will be blinded {17a}

There is no blinding.

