#### Primary outcome

Suicide Ideation – Worst total score (SSI-W) [49]

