### Procedure for unblinding if needed {17b}

Not applicable as no blinding was used in this trial.

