#### Outcome measures

The 19-item Scale for Suicide Ideation – Worst (SSI-W) is an interviewer-administered rating scale [49], which will be used as the measure of the study’s primary outcome as well as to evaluate youth’s eligibility for the study. The SSI-W was adapted from the Scale for Suicide Ideation (SSI)—one of the most widely used instruments developed for rating suicidal ideation to identify the intensity of the most severe suicidal ideation experienced by the person. In this trial, the same questions will be utilized to rate youth’s most severe suicidal ideation during the prior 90 days. The SSI-W has moderately high internal consistency (*α* = 0.88). The scale also has established validity, showing significant associations with other measures of suicidal ideation including the SSI, the suicide item from the Beck Depression Inventory, and the suicide item from the Hamilton Rating Scale for Depression [51]. The primary measure of substance use quantity and frequency will be the interviewer-administered Form 90 Substance Use Interview [50]. This interview yields total number of days, in 90 days prior to last use, of all alcohol/drug use, total number of drugs used, age at first use, lifetime weeks of use, and level of use. This measure also assesses housing, education, and employment days. The Beck Depression Inventory II [51] is the most frequently used self-report instrument for assessment of mood, and cognitive and somatic aspects of depression and has been used with adults and adolescents. The BDI’s internal consistency estimates yielded a mean coefficient alpha of 0.86 for psychiatric patients. The mean correlations of the BDI samples with clinical ratings and the Hamilton Psychiatric Rating Scale were 0.60 and 0.74, respectively [51].

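### No rater masking is planned for an interviewer-rated primary outcome, although no task described for the data collectors needs the allocation

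*Protocol article*

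**What the plan says.** The blinding item {17a} reads "There is no blinding". The unblinding item {17b} confirms it: "Not applicable as no blinding was used in this trial". Neither exempts outcome raters.

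The primary outcome is listed as "Suicide Ideation – Worst total score (SSI-W)". Under Outcome measures, "The 19-item Scale for Suicide Ideation – Worst (SSI-W) is an interviewer-administered rating scale", and "the same questions will be utilized to rate youth’s most severe suicidal ideation during the prior 90 days". The same section describes Form 90, which supplies the substance-use outcome, as interviewer-administered; the BDI-II is self-report. Table 1 schedules all three at baseline and at 3, 6, 9 and 12 months.

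On roles, the Concealment item {16b} says that after baseline "the RA contacts the PI with randomization information, and the PI randomizes the client", and Implementation {16c} says "RAs enroll participants and the PI assigns each participant to a condition". Trial design {8} and Training and supervision give delivery to advocates who work within one condition. Sections {18a} and {19} describe the RAs as trained and supervised for data collection and as entering the questionnaire data. Section {18a} lists training, bi-weekly supervision and quality checks, but no masked or independent rating.

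**The concern.** Youth and advocates cannot be masked in a trial of an added talking therapy. Outcome interviewers are in a different position, because masking them is compatible with the division of labour that the article describes.

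The SSI-W depends on an interviewer's rating of the worst ideation over 90 days. The baseline SSI-W is rated before allocation exists; every later one is rated after it, by someone who may know the arm, in a trial with a directional hypothesis. A rater shift that starts after baseline differs between arms over time, and that is the contrast the Aim 1 growth model tests. Training and quality checks improve consistency but do not remove a systematic shift between arms. If the shift occurs, the planned data cannot measure it or correct for it afterwards. A positive result, which the sponsor would use to support dissemination to drop-in centers, would be open to the objection that unmasked staff rated it.

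**Working it through.** **Who rates, and do they need the allocation?** Recruitment {15} calls the SSI-W rater only the interviewer. That this is an RA is an inference. Section {26a} has RAs obtaining consent, and {15} has the interviewer reviewing consent and then giving the SSI-W. Section {16b} has the RA contacting the PI once baseline is complete, and {18a} and {19} place data collection and entry with RAs. Enrolment, assessment and data entry are the RA tasks described, and none uses the arm.

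**The plan's own figure.** Sample size {14} states power of 0.98 for a slope coefficient of 0.20 with N = 300. The growth and residual variances are not given, so it can be neither confirmed nor refuted. With slope variance 0.10 and intercept and residual variances 0.5 each (assumed), a large-sample calculation gives 0.994 without attrition and 0.985 with it. Masking does not alter this figure, and the point does not depend on it.

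**Illustration of size under a true null.**

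Inputs from the document: 150 per arm; five waves; attrition of 10, 15, 15 and 20%. Assumed: two-sided alpha 0.05; intercept and residual variance 0.5 each, so the baseline SD is sqrt(0.5 + 0.5) = 1; slope variance s² of 0.02 to 0.10 per wave²; monotone dropout; a shift d favouring CTSP + SAU at each follow-up and none at baseline.

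For dropout pattern k with share p_k (last seen at baseline 10%, 3 months 5%, 9 months 5%, 12 months 80%):

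- Z_k = [1, t] with t = 0, 1, 2, 3, 4 up to the last visit; V_k = Z_k diag(0.5, s²) Z_k' + 0.5 I
- Information per arm: J = Σ 150 p_k Z_k' V_k⁻¹ Z_k
- Spurious contrast: J⁻¹ Σ 150 p_k Z_k' V_k⁻¹ b_k, with b = (0, d, d, d, d)
- SE of the slope contrast: sqrt(2 [J⁻¹]₂₂)
- x = spurious slope / SE; rejection = 1 − Φ(1.96 − x) + Φ(−1.96 − x)

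| Shift d | s² | Spurious slope | SE | x | Rejection |
|---|---|---|---|---|---|
| 0.1 | 0.02 | 0.0211 | 0.0332 | 0.636 | 9.7% |
| 0.1 | 0.05 | 0.0213 | 0.0396 | 0.537 | 8.4% |
| 0.1 | 0.10 | 0.0215 | 0.0485 | 0.444 | 7.3% |
| 0.2 | 0.02 | 0.0422 | 0.0332 | 1.272 | 24.6% |
| 0.2 | 0.05 | 0.0425 | 0.0396 | 1.073 | 18.9% |
| 0.2 | 0.10 | 0.0430 | 0.0485 | 0.888 | 14.4% |

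Part of a constant step is taken up by the fitted intercept contrast (about 0.036 for each 0.1 of shift), which Aim 1 also tests.

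**Comparison with a single visit.** At 6 months, 300 × 0.85 = 255 youth and SE = 2/sqrt(255) = 0.125 SD. A shift of 0.1 gives z = 0.80 and 12.6% rejection; 0.2 gives z = 1.60 and 36%. This is not the planned analysis.

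**The case against.** The strongest reply is that open-label conduct is disclosed and contradicts nothing, and that masking would achieve little. The SSI-W rests on what youth say, and they know their arm. The services contact log and the satisfaction questionnaire at each visit can reveal it. Advocates help maintain contact for follow-up, and the research offices are at the drop-in center. An RA unmasked at 3 months stays unmasked for that youth. All of this stands as a limit on the benefit: masking raters removes only the rater's part of the bias, and only for visits where it holds. It does not justify leaving that part in place when no described task needs the allocation.

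Three stronger readings are tempting and are not supported:

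- That the RA learns the arm by calling in the randomisation. Sections {16b} and {16c} have the RA supplying information and the PI randomising and assigning. Neither says that the result returns to the RA. The defect is that nothing prevents it.
- That the false-positive rate becomes 13% or 36%. Those figures are correct for one 6-month comparison of means. The plan specifies a five-wave growth model, for which the inflation is smaller under the variances assumed here.
- That the assumed shifts are a large share of the expected effect. The document gives no single standardised effect to divide by. Against the d of 0.64 to 1.03 that it cites for suicidal ideation, 0.1 to 0.2 SD is about 10% (0.1/1.03) to 31% (0.2/0.64).

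**Conclusion.** The concern holds in this form: the plan rules out masking for every role, including the interviewers who rate the primary outcome and one secondary outcome, and gives no reason why those interviewers should know the allocation. It is a real and avoidable weakness, but it does not invalidate the trial.

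The size is illustrative. The document gives neither the magnitude nor the direction of any rater bias. Under the assumptions listed, a 0.1 SD shift takes the 5% slope test to about 7-10%, and 0.2 SD takes it to about 14-25%, at most roughly five times nominal. The conclusion also rests on two inferences from the split of roles: that the interviewer is an RA, and that RAs do not need the allocation.

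**What to change.** Change {17a} to state that follow-up outcome interviewers are masked to allocation, and adjust {17b} to match. Then:

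- State in {16b} and {16c} that the PI passes the allocation to the assigned advocate and not to the RA.
- Use REDCap user rights to hide arm, session and Working Alliance Inventory fields from RAs.
- Ask youth before each interview not to disclose their arm.
- Administer the SSI-W and Form 90 first, and the services contact log and CSQ last.
- Where staffing allows, have a different RA take later visits for a youth whose RA has been unmasked.
- Record unmasking at each visit and report a sensitivity analysis by masking status. Unmasking happens after randomisation and may differ by arm, so this analysis is supportive only.

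The cost is mainly procedure wording, database permissions and one extra field per visit. Whether interviewers can be swapped without added staff cannot be judged, because the article gives no RA numbers. Any follow-up visits already rated without masking cannot be repaired and should be recorded as unmasked. Masking will be incomplete, and bias in what youth report will remain; the trial report should say both.

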### Procedure for unblinding if needed {17b}

Not applicable as no blinding was used in this trial.

## Data collection and management

### Plans for assessment and collection of outcomes {18a}

Participant data will be collected using REDCap, a secure web application for building and managing online surveys and databases. It is specifically geared to support online or offline data capture for research studies and operations. In order to ensure data quality, all RAs will receive intensive training including videos, in-person trainings, practice, and observation in the field. During the trial, RAs will receive regular supervisions (bi-weekly) and refresher trainings. All assessments will receive quality assurance checks. Outcomes and mediators will be assessed using the following measures.

#### Outcome measures

The 19-item Scale for Suicide Ideation – Worst (SSI-W) is an interviewer-administered rating scale [49], which will be used as the measure of the study’s primary outcome as well as to evaluate youth’s eligibility for the study. The SSI-W was adapted from the Scale for Suicide Ideation (SSI)—one of the most widely used instruments developed for rating suicidal ideation to identify the intensity of the most severe suicidal ideation experienced by the person. In this trial, the same questions will be utilized to rate youth’s most severe suicidal ideation during the prior 90 days. The SSI-W has moderately high internal consistency (*α* = 0.88). The scale also has established validity, showing significant associations with other measures of suicidal ideation including the SSI, the suicide item from the Beck Depression Inventory, and the suicide item from the Hamilton Rating Scale for Depression [51]. The primary measure of substance use quantity and frequency will be the interviewer-administered Form 90 Substance Use Interview [50]. This interview yields total number of days, in 90 days prior to last use, of all alcohol/drug use, total number of drugs used, age at first use, lifetime weeks of use, and level of use. This measure also assesses housing, education, and employment days. The Beck Depression Inventory II [51] is the most frequently used self-report instrument for assessment of mood, and cognitive and somatic aspects of depression and has been used with adults and adolescents. The BDI’s internal consistency estimates yielded a mean coefficient alpha of 0.86 for psychiatric patients. The mean correlations of the BDI samples with clinical ratings and the Hamilton Psychiatric Rating Scale were 0.60 and 0.74, respectively [51].

#### Primary mediator

The Inventory of Cognitive Distortions (ICD) is a 69-item self-report questionnaire designed to assess cognitive distortions in clinical populations [52]. The ICD contains 11 scales, each assessing a distinct cognitive distortion. Each item is rated on a Likert scale from 1 (“never”) to 5 (“always”) and has demonstrated excellent internal consistency reliability (*α* = 0.96). The ICD has also demonstrated strong concurrent validity with measures of dysfunctional attitudes and correlates positively with measures of depression and anxiety [52].

#### Secondary mediators: risk and protective factors

The Social Problem-Solving Inventory-revised Short-version (SPSI-R:S) [53] is one of the most widely used self-report instruments for measuring personal perceptions of social problem-solving ability as it relates to suicidal behaviors. This 25-item assesses both constructive/adaptive and dysfunctional problem-solving dimensions. Strong internal consistency and test–retest reliability (Cronbach’s *α* > 0.90 and *r* = 0.91) and concurrent validity with other measures of social problem-solving and depressive symptomatology have been found [64]. The Coping Inventory for Stressful Situations-Short Form (CISS-SFC) assesses stress coping and includes 21-item measuring that yields 3 subscale scores: task-, emotion-, and avoidance-oriented coping [57]. Reliability for the three subscales is 0.90, 0.88, and 0.83, respectively [57]. Using the Physiologic Stress Measure, we measure chronic physiologic stress of youth through cumulative cortisol levels collected and assayed from hair (each 1 cm of hair growth approximates the cumulative cortisol level for the corresponding month). A recent study assessed the validity of the measure and found cortisol levels assayed in 1 cm of hair were correlated (*r* = 0.61, *p* < 0.01) with salivary cortisol measures in which saliva was collected at 3 time points each day for 1 month [65]. To collect the hair samples, approximately 10–75 mg (approximate width of shoelace tip when bunched) of hair [66] is cut with professional shears from the posterior vertex region of the scalp as close to the scalp as possible. The posterior vertex has the lowest variation in cortisol levels and is the preferred area for sampling [66]. Participants will be surveyed on corticosteroid use as these medications may suppress cortisol levels, psychiatric medication use (e.g., antidepressants), and their hair care practices. Hair will be assayed for cortisol level. The Distress Tolerance Scale (DTS) is a 15-item self-report questionnaire examining the degree to which individuals experience negative emotions as intolerable [56]. The DTS demonstrated high internal consistency and concurrent validity [56]. The Impulsivity Control Scale (ICS) was designed to assess the tendency to engage in impulsive behaviors and lack of patience [58]. The internal reliability for the ICS is 0.80, and the total score was found to be significantly associated with suicidality (*r* = 0.43) and aggressiveness (*r* = 0.63) [58]. The Social Network Inventory (SNI) is a modified version of the Network Interview [55]. The SNI has been used in multiple studies with homeless populations and high-risk adolescents. Respondents are asked to answer various questions about people who are important to them, including family members and friends, and with whom they have interacted within the last 6 months. This study will utilize a support contact measure based on the mean frequency of contact across all network members who the respondent indicated as having provided emotional, tangible, or other support. Possible answers range from 0 to 5 with 0 indicating no contact/support in the past 6 months. This instrument has shown test–retest reliabilities of 0.74 to 0.82 for the key SNI variables for homeless populations [67]. The Interpersonal Needs Questionnaire (INQ) is a 25-item self-report scale designed to assess the two components of suicidal desire as conceptualized by the Interpersonal Psychological Theory of Suicide: thwarted belongingness and perceived burdensomeness [22]. The instrument has demonstrated high internal consistency with alpha coefficients ranging from 0.85 to 0.89 [22]. The Beck Hopelessness Scale (BHS) is a self-report instrument that consists of 20 true–false statements designed to assess the extent of positive and negative beliefs about the future during the past week [54]. The BHS is one of the most widely used measures of hopelessness and has demonstrated high internal reliability across diverse clinical and nonclinical populations with Kuder-Richardson reliabilities ranging from 0.87 to 0.93 [54]. The Acquired Capability for Suicide Scale (ACSS) is a 20-item measure [22], based upon the Interpersonal Psychological Theory of Suicide [21], designed to assess fearlessness about lethal self-injury in both clinical and nonclinical samples. The reliability for the ACSS is adequate (*α* = 0.67) [22]. The ACSS total score is strongly correlated with one item from the Beck Scale for Suicide Ideation (BSS) that asks about one’s courage to kill oneself (*r* = 0.79, *p* = 0.007).

### Plans to promote participant retention and complete follow-up {18b}

One concern when working with YEH is the critical issue of tracking youth for follow-up assessments. Smart and Ogborne [68] in working with YEH suggest the use of outreach workers to maintain contact with those who are lost to follow-up. This proposed project will also utilize the efforts of outreach workers. Extensive locator information will be obtained at the baseline assessment in which youth designate hangout spots in Columbus, as well as collaterals. Each month, the outreach worker will review and update the contact and collateral information which the youth provided. Finally, we have found that YEH who feel connected to staff stay in contact. Also, youth are offered $5 food gift card incentive for attending the intervention sessions.

### Data management {19}

RAs will enter questionnaire data into the RedCap electronic data capture tools via laptop or tablet. The files are saved in a secured fire wall protected server. Any paper records will be entered into RedCap. Data quality will be assessed through range checks for data values. Data will be transferred to a statistical program for analyses.

### Confidentiality {27}

Federal guidelines will be followed regarding the protection of subjects in alcohol/drug studies including using protections offered by the Certificate of Confidentiality. Subjects will be informed that paper records will be kept in a locked and secure records area in the drop-in center offices and transferred to the Ohio State University where they will also be stored in a locked and secure records area. Anonymity will be maintained by labeling materials with identification numbers instead of names.

Electronic data is firewall protected by a Cisco PIX Security Appliance. Cisco’s Adaptive Security Algorithm provides stateful packet inspection firewall services. Authorized network communications are tracked and unauthorized attempts are blocked. The PIX uses the Syslog service to log both inbound and outbound traffic to a Syslog server. Daily logs are monitored daily and stored monthly. All users have passwords that are re-generated and changed every 180 days. Individual files are further protected by user/owner set protection. Only certain users have write privileges on these databases. Backups are run daily on volatile datasets. System-wide weekly and monthly backups are performed.

### Plans for collection, laboratory evaluation, and storage of biological specimens for genetic or molecular analysis in this trial/future use {33}

To collect the hair samples, approximately 10–75 mg (approximate width of shoelace tip when bunched) of hair [65, 66] is cut with professional shears from the posterior vertex region of the scalp as close to the scalp as possible. The posterior vertex has the lowest variation in cortisol levels and is the preferred area for sampling [66]. Hair will be assayed for cortisol at the [name] (Co-I) lab at the Ohio State University.

## Statistical methods

### Statistical methods for primary and secondary outcomes {20a}

Latent growth models (LGM) and mediational models, as described below, will be estimated using MPlus 8 program and evaluated using generally accepted criteria including chi-square, RMSEA, CFI, and SRMR model fit statistics.

#### Study aim 1

The impact of the two study conditions (i.e., CTSP + SAU and SAU alone) on the outcomes will be tested in Aim 1. For suicidal ideation, a latent growth model (LGM) will be applied to the longitudinal data across 5 time points (baseline, 3, 6, 9, 12 months) to estimate the trajectories of change in suicidal ideation over time. Treatment effects on estimated growth parameters, including the intercept (the initial status) and the slope (trends of change over time), will be specifically tested. It is expected that those assigned to CTSP + SAU will show a sharper decrease in suicidal ideation and maintain a lower level following the treatment than those assigned to SAU alone. Similar LGM and follow-up analyses will be conducted on the secondary outcomes, substance use frequency, and depressive symptoms.

#### Study aim 2

To determine the change mechanisms underlying the treatment effects, a series of mediation models will be estimated. Hypothesis 2a tests whether changes in youths’ cognitive distortions will mediate treatment differences on the outcomes. We expect that CTSP will lead to a decrease in cognitive distortions which will predict reduced suicidal ideation (primary outcome) and reduced substance use and depressive symptoms (secondary outcome). Hypothesis 2b tests the proposed risk and protective factors on the association between cognitive distortion and suicidal ideation as well on secondary outcomes. We expect that lower cognitive distortion at the 3-month follow-up will be associated with higher levels of protective factors and lower levels of risk factors at the 6-month follow-up, which in turn will be related to lower suicidal ideation and secondary outcomes at the 12-month follow-up. In these models, the baseline assessment of the mediators and outcomes will be controlled in the analysis. The product of the coefficient of the path from the independent variable to the primary mediator (a), the coefficient of the path from the primary mediator to the secondary mediator (b_1_), and the coefficient of the path from the secondary mediator to the outcomes (b_2_) will be computed as the indirect (mediation) effect between the treatment and outcomes (ab_1_b_2_). The strength and significance of the mediation will be estimated using a bootstrap sampling method. The mediation model for each outcome variable (primary and secondary) will be tested separately.

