### Objectives {7}

In summary, this study focuses on reducing suicidal ideation among YEH who are underserved by the services system. Through this study, we will test our strategy for significantly reducing suicidal ideation (primary outcome), substance use, and depressive symptoms (secondary outcomes) as well as reducing risk factors and strengthening protective factors. Our intervention and conceptual model are based upon Beck’s general cognitive theory [18]. Finally, we will rigorously assess acceptability, feasibility, fidelity, and cost to guide future dissemination efforts. Study aims and hypotheses are listed below:

*Specific Aim 1*. Test the effects of outreach-worker delivered CTSP + SAU versus SAU alone on suicidal ideation (primary outcome), substance use, and depressive symptoms (secondary outcomes) at 3, 6, 9, and 12 months.*Hypothesis*. Youth assigned to CTSP + SAU will show statistically significant improvement on the study outcomes over time compared to those assigned to SAU alone.*Specific Aim 2*. Test the mediating relationship between the intervention and primary and secondary outcomes.*Hypothesis 2a*. Cognitive distortions will mediate the treatment effects on outcomes.*Hypothesis 2b*. The relation between cognitive distortions and outcomes will be further mediated by the risk and protective factors. That is, lower cognitive distortions at the 3-month follow-up will be related to higher levels of protective factors and lower levels of risk factors at 6 months, which in turn will be related to reduced suicidal ideation, substance use, and depressive symptoms at the 12-month follow-up.*Specific Aim 3*. Explore how moderators (baseline service connection, sex, race, sexual orientation) affect individual’s response to CTSP.*Specific Aim 4*. Rigorously assess acceptability, feasibility, fidelity, and cost of outreach-worker delivered CTSP using a mixed-methods approach for future adoption studies.

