### Trial design {8}

The study is designed as a randomized controlled, parallel group, two-arm, superiority trial. All youth (*N* = 300) will be randomly assigned to the cognitive therapy for suicide prevention (CTSP) + SAU (*n* = 150) or to SAU alone (*n* = 150). SAU includes outreach, advocacy, and service linkage and is the standard intervention among providers serving populations experiencing homelessness [35]. The design of this study will allow us to test the intervention as an add-on to standard community-based services (SAU) so that the unique needs of these underserved youth are addressed in a holistic fashion. Advocates will be embedded in condition in order to reduce potential contamination. That is, only advocates trained in CTSP will deliver CTSP + SAU. And finally, as the SAU mirrors that used by shelters and drop-in centers, if the intervention shows significant effects above and beyond SAU, evidence for disseminating the intervention to drop-in centers around the country will be provided. As the intervention is manualized and uses cognitive behavioral strategies, portability is enhanced. SAU and CTSP intervention meetings must be completed by 6 months post-baseline. Self-report questionnaires and interviews will be conducted at baseline and at 3, 6, 9, and 12 months post-baseline. An intent to treat design will be followed so that all youth, regardless of participation in the intervention conditions, will be tracked for follow-up. Please see Fig. 2 below.

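### The primary growth model tests for a treatment effect on pre-randomisation status; if its slope is one linear rate, it also does not fit the predicted fall-then-hold course

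*Protocol article*

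**What the plan says.** The Protocol article, Statistical methods {20a}, Study aim 1, fits a latent growth model to five waves of the suicidal ideation score, with baseline as the first. It then says: "Treatment effects on estimated growth parameters, including the intercept (the initial status) and the slope (trends of change over time), will be specifically tested". The same paragraph predicts that CTSP + SAU youth "will show a sharper decrease in suicidal ideation and maintain a lower level following the treatment than those assigned to SAU alone".

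Three other sections bear on this:
- Sequence generation {16a} places allocation after the baseline measurement: "At the end of the baseline assessment, we will use an urn randomization computerized program".
- Trial design {8} limits the treatment period: "SAU and CTSP intervention meetings must be completed by 6 months post-baseline".
- Sample size {14} gives power of 0.98 for a coefficient of 0.20 on the slope growth factor, described as the growth rate. It gives no power for any other parameter.

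The article does not say whether the slope is linear, piecewise or has free time scores. It also does not say that the arms are held equal at baseline.

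**The concern.** There are two linked problems.

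1. Initial status is measured before anyone is allocated, so treatment cannot affect it. A significant arm coefficient there is either chance or model misfit, yet the plan lists it among the treatment effects to be tested. Estimating a quantity known to be zero also inflates the variance of the slope effect.

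2. The hypothesis is a fall during treatment and then a plateau. A single straight line for the arm difference cannot bend at 6 months. With a free intercept, the fitted line starts above zero at baseline, so part of the real benefit is reported as a difference that existed before treatment.

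At stake are an apparent baseline imbalance that randomisation did not produce and, for some effect shapes and sizes, lost power on the test that matters.

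**Working it through.** **The stated 0.98.** It cannot be recomputed from the article, because alpha and the variances are not given. It is reachable: with assumed intercept variance 0.5, residual variance 0.5, slope variance 0.09-0.10 and two-sided 0.05, power is 0.985-0.990 after attrition.

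**Inputs.** From the article: 150 per arm; attrition 10, 15, 15 and 20% at 3, 6, 9 and 12 months; five waves. Assumed: SD 1, correlation 0.5 between all waves, no random slope, two-sided 0.05, monotone dropout (10% seen at baseline only, 5% to 3 months, 5% to 9 months, 80% throughout), and a true effect of 0.4 SD.

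**Model for the arm difference.** At wave t = 0, 1, 2, 3, 4 the difference is a + b·t. The generalised least squares information is (150/2)·Σ p·X′S⁻¹X, summed over dropout patterns. It gives 118.5 for a, 211.5 for the cross term and 1656 for b.
- Determinant: 118.5 × 1656 − 211.5² = 151,504.
- Slope variance with a free: 118.5/151,504 = 0.000782, SE 0.0280.
- Slope variance with a fixed at 0: 1/1656 = 0.000604, SE 0.0246. This is 23% smaller.
- Intercept variance: 1656/151,504 = 0.01093, SE 0.1045.

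**How much is booked to baseline.** The free-intercept estimate weights the differences at months 0, 3, 6, 9 and 12 by 0.640, 0.369, 0.171, −0.007 and −0.172.
- Complete by 3 months, then held: 0.4 × (0.369 + 0.171 − 0.007 − 0.172) = 0.144 SD. z = 0.144/0.1045 = 1.38, so the test is significant in 28% of trials.
- Linear to 6 months, then held: 0.4 × (0.5 × 0.369 + 0.171 − 0.007 − 0.172) = 0.070 SD. z = 0.67, so 10%.
- Linear to 12 months: 0, so 5%.

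**Slope power**, Φ(b/SE − 1.96):

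| True shape (0.4 SD) | Intercept free | Intercept fixed at 0 |
|---|---|---|
| By 3 months, then held | 0.0838/0.0280 → 0.850 | 0.1022/0.0246 → 0.986 |
| Linear to 6 months, then held | 0.1024/0.0280 → 0.956 | 0.1114/0.0246 → 0.995 |
| Linear to 12 months | 0.1000/0.0280 → 0.947 | 0.1000/0.0246 → 0.983 |

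With random-slope variance 0.02 per wave squared, free-intercept power is 0.72, 0.873 and 0.854 in the same order.

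**At the cited effect size.** For d = 0.64, complete by 3 months and held, free-intercept power is 0.998, or 0.983 with slope variance 0.02. With slope variance 0.05, b = 0.1362 and SE = 0.0396, so z = 3.44 and power is 0.93.

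**Second set of assumptions.** Six variance sets were tuned to return 0.98 when the effect is linear at 0.20 per wave (0.80 at 12 months, in model units). At that 12-month effect:
- Complete by 3 months, then held: planned slope 0.92-0.94, against 0.98-1.00 with the intercept fixed. The intercept test is falsely significant in 49-91% of trials.
- Linear to 6 months, then held: 0.985-0.987 against 0.994-0.999. The intercept test is falsely significant in 16-36%.

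At half that effect, planned power is 0.40-0.42 against 0.51-0.68 for the first shape, and 0.54-0.55 against 0.61-0.71 for the second.

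**The case against.** The strongest defence is that the article never says linear. It commits to judging models by fit statistics, and time scores are ordinary analysis-plan detail. A piecewise or free-time-score model would remove the misallocation. That stands, so the second half of this point is conditional. It does not rescue the intercept test, which is misplaced under any growth form.

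A reader might infer more than the documents support:
- *The slope test is weakest under the predicted shape.* Not established. If the effect builds over the 6-month treatment period and is then held, which is a close reading of the hypothesis, the single slope does slightly better than under a linear effect (0.956 against 0.947). The score rates the worst point of the prior 90 days, which makes a full effect at 3 months demanding. A fading effect would cost more, but it contradicts the stated expectation of maintenance.
- *Either parameter could be declared the primary result.* Overstated. Sample size {14} powers only the growth rate, and the Aim 3 moderation analysis concerns outcome slopes, so the slope is recognisable as the efficacy parameter.
- *Selecting youth on a high entry score pushes treatment effect into the intercept.* It does not. That fall is common to both arms and cancels from the comparison if attrition is similar.
- *Leaving out the urn factors as covariates, or visit-specific contrasts, is an error.* Both are commonly left to the analysis plan.

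**Conclusion.** The point holds in a limited form and should be fixed. Testing treatment on initial status is wrong as stated, because baseline precedes randomisation. Fixing that effect at zero raised slope power in all three shapes tabulated, including the truly linear one.

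The misallocation of 0.07-0.14 SD and the 10-28% false intercept findings rest on a linear slope, a 0.4 SD effect, correlation 0.5 and no random slope. The power cost depends on shape and effect size. It is largest for an early drop of modest size (0.850 against 0.986). For a maintained effect at the cited d of 0.64 or more it is negligible without a random slope and small at slope variance 0.02. It becomes visible only with an early full drop and large slope variance. The documents do not show that the trial is underpowered.

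**What to change.** 1. Delete the treatment test on the intercept, and fix the arm effect on baseline status at zero.
2. State the growth form, and choose one that can represent a fall followed by a plateau. A piecewise slope with a knot at 6 months is one option.
3. Name one primary treatment contrast, for example the model-implied mean difference over 3-12 months, and restate power for it with the variances and alpha assumed.

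The cost is wording in the protocol and analysis plan, plus a new power calculation. The statistical downside is modest. If the effect is truly linear, the mean contrast has power 0.91 (unstructured visit means) to 0.94 (piecewise), under the assumptions in the table. The planned slope has 0.95, and a single slope with the intercept fixed has 0.983. The exact knot and contrast are for the investigators to choose; what matters is that they are fixed in advance.
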